### Data collection

Local research staff will prospectively collect data on all available eligible episodes of threatened preterm labour.

Key data for all patients (at control and interventions sites)Hospital numberGestation at presentationQuantitative fetal fibronectin values (if available)Cervical length measurements (if available)Current NICU availabilityIUT attempt planned.Patient characteristics (age, parity, ethnicity, risk factors for preterm labour)Outcome data as outlined above (5.1 and 5.2).

Anonymised participant data will be transcribed on to the study database prepared for the trial by MedSciNet (Stockholm, Sweden).

Anonymous data will be stored on the Preterm Clinical Network (PCN) Database (REC Ref. 16/ES/0093). Identifiers (initials, date of birth, hospital and NHS number) required to ensure accurate outcome data collection will be stored on the separate, but linked, PCN Patient Details Database which is only accessible to local site users.

Women will be followed up until postnatal discharge. Neonates will be followed up to discharge or 28 days (whichever is sooner). Local research staff will monitor expected dates of delivery and ensure timely collection of pregnancy outcomes. Outcome data (medical and economic) will be collected by review of obstetric handheld/electronic notes. Outcome data for women who are transferred outside their local unit will be obtained by contacting the referral hospital. The Emergency Bed Service and Neonatal Transport Service are supportive of the study and can assist us in tracking patients who are not accommodated in their local hospital.

For the health economics analysis data will be collected from routine medical records on antenatal admissions, length of stay, outpatient appointments, day cases and scans for women identified as participants in the trial from the time of first being identified as part of the trial until discharge following delivery. Healthcare resource group codes for each event will be collected and costs from National Reference costs applied. We will conduct a time and motion study of clinician time and resources spent identifying a suitable transfer location on a sample of transfers. We will also conduct a micro costing of the cost of a transfer. We will also collect and report statistics and costs per patient for mode of delivery for women identified as participants in the trial and ex-utero transfers and NICU stays for their neonates (adjusting for non-singleton births). We will include the cost of the intervention which will include the cost of any training and the cost of clinician time associated with using the app. This information will be collected from the app, patient notes and a time and motion questionnaire administered to clinicians for a subset of patients.

For the women’s experience study (EQUIPTT-Q) participants, following consent, the researcher will enter the woman’s initials, hospital number, date of birth and date of signing consent against the next consecutive EQUIPTT-Q ID number on the EQUIPTT-Q register. This ID number will be entered on the consent form and alternative pages of the questionnaire booklet. The participant will be asked to complete part 1 (questions regarding baseline demographics, her symptoms and anxiety levels prior to assessment) straight away. She will be asked to keep the booklet with her and to complete part 2 (tests, planned interventions, anxiety post assessment and decisional conflict scale questions) after her clinical assessment. She will then hand the completed booklet back to staff before leaving the unit. The researcher checks the booklet for completion and enters data on EQUIPTT-Q datasheet (spreadsheet). The datasheet (which contains no identifiable data) is emailed to trial management team on a weekly basis. Data will be merged into the EQUIPTT-Q SPSS database which is separate from the main trial database.

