#### Health economics evaluation

For the health economics analysis, a multi-level general linear model using appropriate family and link function, will be used to calculate the average cost per participant of use of the QUIPP app for triage and transfer compared to current practice. Costs will also be reported alongside secondary clinical outcomes as part of a cost-consequences analysis. We are not conducting a cost per quality adjusted life year (QALY) analysis (also called cost-utility analysis) given the hypothesis that the intervention is cost saving and does not result in any health decrement. These assumptions make a cost per QALY analysis redundant. Any health improvement will be captured by adverse incident reporting and secondary maternal and neonatal clinical outcomes, which will be reported alongside costs as part of the cost-consequences analysis.

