### Implementing the QUiPP app intervention

In each phase, each cluster will recruit consecutive women with singleton or twin pregnancies presenting between 23^+ 0^ and 34^+ 6^ weeks presenting with symptoms of preterm labour. Eligible participants will be identified at labour ward and day assessment triage by the direct care team and local research support teams. Inclusion and exclusion criteria are defined above.

All sites will receive training on the use of the QUIPP App and management guidance prior to its introduction, and periodically throughout the trial at peaks of staff turnover. This training will be delivered by the trial team at different times and locations to suit each site, for example, at departmental audit meetings and staff induction. Training will be delivered via clinical vignettes which provide opportunity for the clinicians to use the app in a training environment. Aide-memoires such as lanyards and pens are provided to each site to encourage use of the app. The doctor/midwife assessing the woman inputs the gestation, previous history of late miscarriage or preterm birth, quantitative fetal fibronectin value and/or ultrasonic cervical length into the app and the app provides % risk of delivery within 1/2/4 weeks and before 30/34/37 weeks. The exact thresholds for admission or treatment are gestation-dependent and may need to be tailored to individual circumstances. However as a recommendation, our guidance will suggest a 5% risk of delivery within 7 days as threshold for antenatal corticosteroid administration, admission, and/or in-utero transfer. Ultimately however the management decisions following the knowledge provided by the QUIPP app will remain the clinicians’ responsibility. A feedback option is available on the app to directly contact the trial team with specific non-clinical queries. Incentives and competitions will also aim to increase recruitment for the qualitative recruitment.

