#### Secondary outcomes

Secondary outcomes will include:All components of primary outcome individuallyMaternal clinical outcomes (e.g. new onset gestational diabetes, thromboembolic disease and confirmed sepsis)Neonatal clinical outcomes (e.g. neonatal death prior to discharge, gestational age at delivery, birthweight, days of supplemental oxygen)Process measures (days of maternal hospitalisation, steroid, tocolytic and magnesium sulphate administration, neonatal intensive-care admissions, ex-utero transfer within 24 h of delivery)Compliance to management recommendations

Information will also be collected on the number of preterm deliveries before 34, and 37 weeks, and on the use of treatments to prevent prematurity [antibiotics, cerclage (by site), progesterone]. The authors may be contacted for samples of the data collection forms.

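### The 28-day cap on neonatal follow-up cannot deliver two named neonatal outcomes, death before discharge and total oxygen days, and it leaves the NICU costing window unclear

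*Protocol article*

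**What the plan says.** All references are to the protocol article.

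- **Neonatal window (Data collection).** "Neonates will be followed up to discharge or 28 days (whichever is sooner"). This is the only neonatal follow-up window stated. Its starting point is not given; I read it as birth.
- **Maternal window (same section).** "Women will be followed up until postnatal discharge", with no day limit.
- **Neonatal outcomes (Secondary outcomes).** The examples listed are "neonatal death prior to discharge, gestational age at delivery, birthweight, days of supplemental oxygen". None carries a 28-day limit.
- **Neonatal cost items (Data collection, health economics paragraph).** Statistics and costs are to be reported for "ex-utero transfers and NICU stays for their neonates", with no end date. In the same paragraph the mother's resource use is collected from routine records until she is discharged after delivery.
- **Role of these outcomes (Health economics evaluation).** A cost per QALY analysis is omitted "given the hypothesis that the intervention is cost saving and does not result in any health decrement". Health effects are to be picked up through adverse incident reports and the secondary maternal and neonatal outcomes, reported next to costs.
- **Population (Implementing the QUiPP app intervention).** Consecutive women with "singleton or twin pregnancies presenting between 23^+ 0^ and 34^+ 6^ weeks".

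**The concern.** A follow-up rule has to be at least as long as the outcomes it feeds. Here it is not. A baby who dies in hospital on day 35 has died before discharge, but outside the follow-up window. A baby on oxygen until day 60 contributes at most 28 oxygen days.

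This matters more than a labelling slip usually would, for two reasons. First, the app supports withholding admission, steroids and transfer when predicted risk is below 5%, and the Discussion weighs a missed imminent delivery as 19 times as harmful as overtreatment. The neonatal outcomes are where the consequences of a missed delivery would show. Second, the economic analysis leaves out QALYs on the hypothesis of no health loss and relies on these secondary outcomes to show the health effects. If they stop at day 28, that hypothesis is examined least completely in the infants with the longest stays.

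**Working it through.** No sample size, power or alpha figure depends on the neonatal window, so there is no plan figure to reproduce. The check is a comparison of windows, followed by date arithmetic.

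**1. Windows side by side, for an infant still in hospital on day 28**

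| Item | Period implied by its wording | Period covered by stated follow-up | Match? |
|---|---|---|---|
| Death before discharge | Birth to discharge | Birth to day 28 | No |
| Days of supplemental oxygen | No limit given | Birth to day 28 | No |
| NICU stay and its cost | No limit given | Not stated separately; day 28 if the general rule applies | Unclear |
| Gestational age at delivery, birthweight | At birth | Covered | Yes |
| Ex-utero transfer within 24 h | First day | Covered | Yes |

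For an infant discharged by day 28, every row matches. The problem is confined to longer stays.

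**2. How mature an infant is when follow-up stops**

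Postmenstrual age at day 28 = gestation at birth + 4 weeks:

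- born at 23+0: 27+0
- born at 26+0: 30+0
- born at 28+0: 32+0
- born at 32+0: 36+0
- born at 34+6: 38+6

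**3. Share of the stay that falls after day 28**

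Inputs: the 28-day cap (Data collection), gestations at birth from 23+0 (the lower limit for presentation), and an assumed discharge age. The article gives no length of stay, so discharge is varied from 34 to 40 weeks postmenstrual age.

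Stay = (discharge age − gestation at birth) × 7 days. Days lost = max(0, stay − 28). Share lost = days lost / stay.

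| Birth | Discharge at 34 wk | Discharge at 36 wk | Discharge at 40 wk |
|---|---|---|---|
| 23+0 | 49/77 = 64% | 63/91 = 69% | 91/119 = 76% |
| 26+0 | 28/56 = 50% | 42/70 = 60% | 70/98 = 71% |
| 28+0 | 14/42 = 33% | 28/56 = 50% | 56/84 = 67% |
| 30+0 | 0/28 = 0% | 14/42 = 33% | 42/70 = 60% |
| 32+0 | 0/14 = 0% | 0/28 = 0% | 28/56 = 50% |

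Whichever discharge age is assumed, the share lost is largest at the earliest births. From about 30 weeks it depends almost wholly on the assumption.

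**4. Effect on the comparison between arms**

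Let L be the mean number of days per infant falling after day 28 in an arm. Then

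observed difference (app − control) = true difference − (L_app − L_control).

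If the two L values are equal, the difference in means is unchanged. If app sites have more late days, extra harm and cost at app sites are understated. If app sites have fewer, a benefit and a NICU saving are understated. The article gives no information on either L, so the sign cannot be determined. Deaths after day 28 behave in the same way.

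**The case against.** **The economic window may be separate.** The health economics paragraph names its own source, routine records, and puts no end date on NICU stays. A reader might infer that NICU cost is definitely truncated at day 28. The article does not say that. Equally, it does not say that collection runs on to discharge, and the only neonatal window it states is the capped one. So NICU cost may be truncated; that is as far as the text goes.

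**The cap treats both arms alike.** A reader might also infer that it biases safety towards no difference and cost towards savings. That would require more long-stay infants at app sites. The protocol hypothesises better selection for admission and transfer, under which the cap would hide benefit instead. It also attributes savings to fewer inappropriate admission and transfer decisions, not to NICU days. The objection stands: no direction can be claimed.

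**Neonatal death can be read strictly as death within 28 days.** On that reading the death outcome might fit the window. But the stated endpoint is discharge, and oxygen days are cut short on either reading.

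**The article is a condensed account.** Its neonatal outcomes are examples, and it refers to outcome section numbers it does not contain, so the full protocol may define time limits. That would excuse silence. Here the article states both a window and the outcomes, and they disagree.

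**Few infants may be affected.** This stands. Most women with threatened preterm labour do not deliver within a week, and eligibility runs to 34+6. The number of infants still in hospital at day 28 is not given and cannot be derived.

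**Conclusion.** The point holds as an inconsistency in secondary safety outcomes. As written, follow-up cannot deliver death before discharge or total oxygen days for infants still in hospital on day 28, and the window for NICU days and cost is unclear. For discharge between 34 and 40 weeks postmenstrual age, 64% to 76% of the stay is unobserved for birth at 23+0, 33% to 67% at 28+0 and 0% to 50% at 32+0. These ranges rest on the assumed discharge ages and on counting the 28 days from birth. They describe individual infants and are not an effect on the trial result.

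The consequence is a less complete neonatal safety comparison, in the outcomes that the economic analysis relies on to show health effects. The documents do not support a claim that the cap favours the app. The primary outcome, which rests on a 7-day delivery interval and transfers around delivery, and the sample size of 580 are untouched. The matter should be corrected, but it does not threaten the main analysis.

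**What to change.** **Preferred.** Remove the 28-day cap for three items: death, days of supplemental oxygen and NICU days. Collect each to hospital discharge, including from any unit to which the mother or baby was transferred. The cost is a later data lock and some retrieval of neonatal records for the few infants still in hospital at day 28. The retrieval is a modest addition, because the planned review is of obstetric notes and the contact with other hospitals is described for transferred women.

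**Otherwise, change the wording only.** Define the outcomes as *death by day 28 or discharge, whichever is sooner* and *oxygen days to day 28*. State the window used for NICU days and cost, and the origin of the 28 days. Say that later harm and cost are not counted in either arm, and limit the safety and cost conclusions to that window. This needs no further data collection, but longer-term neonatal harm stays outside what the trial can report.

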### Sample size

For inappropriate admission decisions, a total sample size of 580, approximately 50 recruits per site, was calculated. Data from our group’s ongoing prospective observational study into the ability of qfFN to predict preterm birth in symptomatic women (PETRA REC Ref. 14/LO/1988) has allowed us to estimate the likely treatment effect for the intervention reducing inappropriate admissions from 25 to 10% and intra-class correlation 0.030. Based on 13 clusters this treatment effect requires approximately 580 for 80% power. We are aware that a larger number of centres would also be preferable, but believe 13 is adequate and at the limit of what is currently feasible.

For our qualitative questionnaires, we have estimated a target recruitment of 300 participants, 25 recruits per site, allowing for non-compliance and data collection errors. Based on previous research involving visual analogue scale (VAS) scores [19], a total sample size of 272 was required at standard levels of significance (alpha = 0.05 two-sided) to achieve 90% power to detect a 10% difference in mean VAS scores between hospitals with and without the intervention.

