#### Women’s experience study (EQUIPTT-Q)

When feasible (i.e. participants identified prior to assessment and staff available to obtain consent), participants in the cluster randomised trial will be invited to complete a questionnaire booklet. This includes questions about her symptoms, anxiety levels before and after her clinical assessment, the tests she received, her options for further management and the extent to which she is content with the decisions made. Anxiety levels and decisional conflict will be ascertained by visual analogue scale (VAS), and the Decisional Conflict Scale (DCS) questions [19]. The questionnaire booklet has been designed in collaboration with the Women’s Health Academic Centre’s Preterm Birth Studies public and patient involvement (PPI) panel. Difference in VAS anxiety scores between women before and after assessment, and between hospitals with and without QUIPP app in use at the time of assessment, will be calculated (paired and independent samples t-test). Difference between DCS scores after assessment, between hospitals with and without QUIPP app in use, will also be calculated (paired and independent samples t-tests as appropriate). If the DCS and VAS data is found to be not normally distributed, non-parametric equivalent tests will be used.

A subgroup of participants (approx. 20–30) will be invited to provide a more in-depth account of their experiences during one-to-one face-to-face or telephone interviews. The interview schedule will be determined following interim analysis of the data and free text box comments. The Framework approach [20] will be used to analyse the qualitative data obtained from the interviews. This method of qualitative data analysis is suitable for use with the anticipated findings from this study. Data will be analysed using NVivo software.

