#### Women’s experience study (EQUIPTT-Q)

Our key outcome is difference in VAS anxiety scores between women before and after assessment, between hospitals with and without QUIPP app in use at the time of assessment. We will also analyse difference between DCS scores after assessment, in hospitals with and without QUIPP app in use.

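### The post-assessment anxiety score has no fixed time, and its only stated outer limit, leaving the unit, depends on the management the app is meant to change

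*Protocol article*

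**What the plan says.** The Protocol article describes the booklet under Data collection. Part 1 follows consent directly: the woman gives baseline details, symptoms and "anxiety levels prior to assessment) straight away". She then keeps the booklet and is asked to "complete part 2 (tests, planned interventions, anxiety post assessment and decisional conflict scale questions) after her clinical assessment". The next sentence is the only one that bounds the other end: "She will then hand the completed booklet back to staff before leaving the unit".

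The Outcomes section shows what rests on these two measurements: "Our key outcome is difference in VAS anxiety scores between women before and after assessment", compared between hospitals with and without the app. The Decisional Conflict Scale is collected only in part 2, so it has no baseline. Under Data analysis, the VAS differences "will be calculated (paired and independent samples t-test"), with non-parametric equivalents as fallback. The article states no term for elapsed time.

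The section on implementing the app gives a 5% risk of delivery within seven days as the suggested "threshold for antenatal corticosteroid administration, admission, and/or in-utero transfer".

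**The concern.** The before score is tied to a moment that is the same for every woman. The after score has a common starting point but an end point that moves with what happens to her next. A woman sent home reaches that end point soon after the plan is made. One waiting for transfer, or admitted within the same unit, may reach it hours later, after treatment, monitoring or further tests.

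The app is intended to change who goes home, who is admitted and who is transferred. If it does, the mix of permitted windows differs between arms. A between-hospital difference in VAS change, or in decisional conflict, could then partly reflect elapsed time or stage of care rather than the app. If completion times are not recorded, such a difference could be neither detected nor adjusted for later.

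**Working it through.** **1. Permitted window for part 2.** All entries come from the Data collection section except the transfer time, which is from the Background section on in-utero transfer.

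| Woman is | Earliest time | Latest time |
|---|---|---|
| Sent home | After assessment | Departure, shortly after the plan is made |
| Transferred | After assessment | Departure to the other hospital; arranging and completing a transfer is said to average 340 min (about 5 h 40 min) |
| Admitted | After assessment | Move to a ward or discharge, depending on what *unit* means |

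The first column of times does not vary by disposition. The second does.

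**2. Meaning of *unit*.** The sub-study text does not define it. Elsewhere the article mostly uses the word for the hospital or maternity unit: in the Background on transfers, in Trial design for the control units, and in Data collection for women moved out of their local unit. On that reading an admitted woman's window could run through her stay. If it means only the triage area, the window closes when she moves to a ward.

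**3. How timing could enter the contrast.** Let *p* be the share of women with a given disposition, and *s* the average change in VAS from completing part 2 at the time typical of that disposition rather than straight after the plan is explained. If *s* depends on disposition only,

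bias = sum over dispositions of (*p* in app hospitals − *p* in control hospitals) × *s*.

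The article gives neither *p* nor *s* for sub-study participants.

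**4. The sample-size section does not supply *p*.** It refers to "reducing inappropriate admissions from 25 to 10" per cent, a fall of 25 − 10 = 15 points. The Outcomes section defines an inappropriate admission decision in two directions: admitted but delivering after more than seven days (call this rate A), or not admitted but delivering within seven days (rate B). If the timing of delivery is unchanged, the change in the share admitted equals change in A − change in B. Two illustrative splits of the same 15-point fall (assumptions):

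- A falls by 15, B unchanged: admissions fall by 15 points.
- A falls by 10, B falls by 5: −10 − (−5) = −5, so admissions fall by 5 points.

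The 15 points therefore do not fix the difference in admissions.

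**5. The VAS sample size as a yardstick.** The article gives a total of 272 for 90% power, two-sided alpha 0.05 and a 10% difference in mean VAS. It states no standard deviation, so 272 cannot be reproduced independently. Reading 10% as 10 points on a 0–100 scale (assumption), with 136 per arm and clustering ignored, the implied value is

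SD = 10 × √(136/2) / (1.960 + 1.282) ≈ 25.4.

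At that SD, a bias of 1 point against a true 10-point effect would lower power from 90% to about 83%, and a bias of 3 points to about 62%. With no true effect, the same biases would give false-positive rates of about 6% and 16%. These figures show how sensitive the comparison is. They do not estimate the bias, and the point does not depend on them.

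**The case against.** The strongest reply is that the sentence about leaving governs return of the booklet, not its completion. Completion is tied to the clinical assessment, an event common to both arms and to every disposition. Part 2 also asks about planned interventions, which suggests that it is meant to be filled in once the plan is known and before it is carried out. This stands to the extent that only the latest permitted time is shown to depend on disposition; that women actually complete it late is an inference. It does not close the gap, because no interval after assessment is stated and the woman keeps the booklet until she leaves.

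Second, the booklet and full protocol are not shown, and either may carry a completion instruction or a time field. This also stands: it cannot be said that no time is recorded.

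Third, anxiety that changes because a woman learns she is going home is a genuine effect of the app. Agreed; only differences in elapsed time or stage of care would be artefact.

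A reader might go further in three ways that the article does not support:

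- That both scores are untimed. Part 1 has a set time.
- That transferred women will leave without completing part 2. No return rate is given, and an average of 340 min for a transfer points to delay rather than abrupt departure.
- That the bias can be sized by multiplying the 15-point fall by an assumed VAS shift. The 15 points are a two-way decision rate, and the shift has no source in the article.

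**Conclusion.** The point holds as a weakness in a stated procedure. The window allowed for the key outcome of the women's experience sub-study, and for the Decisional Conflict Scale, ends at an event that depends on management, and management is what the intervention targets. The window can therefore differ between arms.

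No size or direction of bias can be derived from the article, and none is claimed. The conclusion rests on two things: that the article's wording is the operative instruction, and that *unit* is read, as mostly elsewhere in the article, as the hospital or maternity unit. If it means only the assessment area, the window for admitted women shrinks, although that for women awaiting transfer may still be long. The trial's primary outcome, inappropriate management, is untouched. This is a low-cost improvement, not a demonstrated error.

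**What to change.** In the Data collection section, state that part 2 is completed and collected once the management plan has been explained to the woman and before she goes home, to a ward or to another hospital. Have the completion times of parts 1 and 2 written in the booklet, if it does not already provide for this. Report the interval between the two parts and the booklet return rate by arm, so that any difference in timing or return can be seen beside the VAS and decisional conflict results.

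The cost is one added instruction to site staff and two time fields.
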